#### Inclusion criteria for healthy participants

3.3.3.

Participants who meet all of the following criteria will be included as normal control: (1) right-handedness and age ≥ 50 years and < 80 years; (2) no cognitive impairment according to Jak/Bondi criteria (non-subjective cognitive decline/MCI/dementia) and normal daily living ability (a Functional Activities Questionnaire [FAQ] score < 9); (3) no contraindications to MRI scanning, such as pacemaker implantation, metal fixed dentures; and (4) volunteering to cooperate and signing an informed consent form.

#### Exclusion criteria for healthy participants

3.3.4.

Participants who meet any of the following criteria will be excluded from the normal control group: (1) claustrophobia; (2) severe cranial anatomical asymmetry or definite lesions found in MRI; (3) regularly use of probiotics, prebiotics, or antibiotics; or (4) participation in other clinical trials.

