#### Inclusion criteria for patients with aMCI

3.3.1.

Patients who meet the following criteria will be included: (1) diagnosis of aMCI according to the Jak/Bondi 2014 diagnostic criteria (33); (2) right-handedness and age between 50 and 80 years; (3) disease course ≥6 months; (4) a Clinical Dementia Rating (CDR) score of 0.5; (5) a Hachinski Incheinic Score (HIS) ≤ 4; (6) education level ≥ 8 years (including vocational education); (7) volunteering to cooperate and signing an informed consent form; and (8) no contraindications to MRI scanning, such as pacemaker implantation, metal fixed dentures.

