#### Exclusion criteria for patients with aMCI

3.3.2.

Patients who meet any of the following criteria will be excluded: (1) receiving treatment that interferes with cognitive function (e.g., management of acute psychotic episodes, such as memantine, rivasmine, donepezil); (2) a history of neurological conditions affecting cognitive function confirmed by examination, except in patients with suspected early AD, including Parkinson’s disease, vascular dementia, brain tumour, traumatic brain injury, or other diseases which might lead to neurological injury and abnormal brain structure; (3) presence of a systemic diseases that could cause cognitive decline, such as anaemia, Hashimoto’s encephalopathy, metabolic encephalopathy, hepatic encephalopathy, renal encephalopathy; (4) infection, other focal injury, multiple or important brain memory area infarcts, or severe leukodystrophy (Fazekas score ≥ 3) indicated by brain MRI; (5) a history of tumour, psychiatric illness (e.g., bipolar disorder, schizophrenia) or severe depression (Hamilton Depression [HAMD] scale score ≥ 24) and anxiety (Hamilton anxiety [HAMA] scale score ≥ 29); (6) haemorrhagic disease, bleeding tendency or severe skin infection; (7) severe drug dependence, smoking, drug or alcohol abuse; (8) pregnant, potentially pregnant, or lactating females; (9) receipt of any acupuncture therapy or participation in other clinical trials during the 6 months prior to enrolment; and (10) regularly use of probiotics, prebiotics, or antibiotics.

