#### Healthy participants

3.6.2.

The healthy participants will not receive any treatment. Matched healthy individuals without cognitive impairment will be determined based on their medical history and cognitive function tests. The general information and cognitive assessment results will be recorded. fMRI images, faecal samples and fasting blood samples of healthy participants will be acquired at enrollment.

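### Healthy controls are selected under looser criteria than patients and compared without covariates, which leaves the exploratory aMCI-versus-healthy contrast open to confounding in either direction

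*Protocol article*

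**What the plan says.** **Controls.** Section 3.3.4 excludes a healthy participant for any of four reasons: "1) claustrophobia; (2) severe cranial anatomical asymmetry or definite lesions found in MRI; (3) regularly use of probiotics, prebiotics, or antibiotics; or (4", where the fourth item is enrolment in another trial. Section 3.3.3 requires "right-handedness and age ≥ 50 years and < 80 years", no cognitive impairment (including no subjective decline), an FAQ score below 9, no MRI contraindication, and consent. It sets no education minimum.

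**Patients.** Section 3.3.1 requires "education level ≥ 8 years (including vocational education"). Section 3.3.2 lists ten exclusions. Among them are "1) receiving treatment that interferes with cognitive function", "3) presence of a systemic diseases that could cause cognitive decline, such as anaemia", "5) a history of tumour, psychiatric illness (e.g., bipolar disorder, schizophrenia) or severe depression" (the same item also bars severe anxiety) and "severe drug dependence, smoking, drug or alcohol abuse".

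**Matching.** The Abstract describes the healthy volunteers as matched. Section 3.6.2 says: "Matched healthy individuals without cognitive impairment will be determined based on their medical history and cognitive function tests". Neither place names a matching variable. Section 3.4 confirms that controls are not randomised.

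**Analysis.** Section 3.11 assigns inter-group comparison of scale scores, brain function, microbiota and cytokines to an independent-samples t-test or, for non-normal variables, the Mann–Whitney U test. Multiple linear regression is named only for the correlation analysis. The significance threshold is 0.05.

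**Use.** The Discussion uses the aMCI-versus-healthy differences to look for biomarkers and to describe the gut-brain features of aMCI.

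**The concern.** In a comparison without randomisation, only design (common eligibility, matching) or analysis (covariates) protects against differences unrelated to the disease. As printed, a smoker, a person with anaemia or a person with a psychiatric history could meet every control criterion while being barred as a patient. Such characteristics plausibly bear on cytokines, gut microbiota or fMRI signals, and these are the measures being compared.

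The article itself treats some of the factors as relevant. The Discussion links gut microbes to mood disturbance, and Section 3.8.1 gives MoCA-B cut-offs that depend on education. A difference attributed to aMCI might therefore reflect who was allowed into each group. Equally, controls in poorer health could mask a real difference. This comparison is the stated reason in the Discussion for enrolling the 20 controls.

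**Working it through.** The plan gives no effect size, SD or power for this comparison (Section 3.5 argues from precedent), so there is no figure to reproduce. The check has two parts.

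**1. Criteria side by side**

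| Patient exclusion (3.3.2) | Counterpart for controls (3.3.3, 3.3.4) |
|---|---|
| (1) cognition-affecting treatment | none |
| (2) neurological disease | partial: MRI lesions |
| (3) systemic disease | none |
| (4) infection, infarcts or white-matter disease on MRI | partial: MRI lesions |
| (5) tumour, psychiatric illness, severe depression or anxiety | none |
| (6) bleeding tendency, skin infection | none |
| (7) smoking, drug or alcohol abuse | none |
| (8) pregnancy, lactation | none |
| (9) prior acupuncture or other trials | partial: other trials only |
| (10) probiotics, prebiotics, antibiotics | full |

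Count: 1 full + 3 partial + 6 none = 10. Of the six, (6) mainly concerns needling safety and (8) hardly arises at age 50 or over. That leaves (1), (3), (5) and (7) as the ones that matter, plus the education minimum.

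**2. What a residual imbalance would do**

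Inputs from the document: 40 patients (20 + 20) and 20 controls (Section 3.5); threshold 0.05 (Section 3.11), taken as two-sided because sidedness is not stated.

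Assumptions: common SD of 1; an uncontrolled factor shifts the group difference by b SD. The values of b are not in the documents.

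- Standard error of the difference: √(1/40 + 1/20) = √0.075 = 0.274 SD.
- Noncentrality: b / 0.274, on 40 + 20 − 2 = 58 degrees of freedom.
- False-positive rate when the true aMCI effect is zero: probability that a noncentral t falls outside the two-sided 5% limits.

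| b (SD) | b / 0.274 | 40 vs 20 | 20 vs 20 |
|---|---|---|---|
| 0 | 0 | 0.050 | 0.050 |
| 0.1 | 0.36 | 0.065 | 0.061 |
| 0.2 | 0.73 | 0.111 | 0.095 |
| 0.3 | 1.09 | 0.190 | 0.152 |

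(The 20 vs 20 column applies if one trial arm is compared with the controls; its rates use its own standard error and degrees of freedom.)

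How b might arise: a factor 20 percentage points more common in one group that shifts a marker by 0.5 to 1.0 SD gives b = 0.20 × 0.5 = 0.10 up to 0.20 × 1.0 = 0.20, hence 6.5% to 11.1%.

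Opposite direction, same method: with a true difference of 0.8 SD, power at 40 vs 20 is 0.819. If confounding pulls it back by 0.3 SD, the apparent difference is 0.8 − 0.3 = 0.5 SD and the chance of detecting it falls to 0.435.

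**The case against.** The strongest reply is that the control criteria do more than the count suggests. Excluding any subjective or objective cognitive impairment and requiring normal daily function makes it unlikely that a control takes an anti-dementia drug or has an encephalopathy. MRI lesions catch much structural neurological disease. This stands in part, but it does not reach smoking, alcohol, tumour, psychiatric history or milder systemic disease such as anaemia.

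Second, the controls are called matched, and Section 3.6.2 refers to medical history. A reader might infer from that sentence that matching is confined to history and cognitive tests and leaves out demographics. The text does not support this: it says how healthy status is determined and rules out no matching variable. The variables may be named in the full protocol. Matching on demographics would still not remove the written difference in health and lifestyle criteria.

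Third, covariates for a secondary comparison are often left to an analysis plan, which is not shown. That is fair as to detail. Section 3.11 does, however, name specific tests for inter-group comparison, and neither of them takes covariates.

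Fourth, two contrasts are smaller than they look. Patients are excluded for depression only at HAMD 24 or above, so patients scoring 17 to 23, which Section 3.8.1 classes as depression, remain eligible. HAMD and HAMA are measured in controls (Table 1), so an imbalance would be visible. The age limits (50 to 80 against 50 to below 80) differ only at the upper boundary, which is trivial. Both points stand.

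**Conclusion.** The point holds as a risk of confounding in the exploratory, non-randomised comparison of aMCI with healthy participants. The printed criteria omit four relevant patient exclusions and the education minimum for controls, the matching variables are unnamed, and the stated tests do not adjust.

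A reader might go further and conclude that these differences are confounded, or will be falsely positive. The documents do not support that. They give neither the prevalence of any barred condition among controls nor its effect on a marker, and with no residual imbalance the error rate stays at 5%. The range of about 6.5% to 19% depends wholly on the assumed 0.1 to 0.3 SD, and the bias could as easily conceal a difference.

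The randomised acupuncture-versus-waiting-list comparison and the ADAS-cog primary outcome do not involve the controls and are unaffected. This is something the sponsor should correct, but it does not threaten the trial's main result.

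**What to change.** 1. In Sections 3.3.3 and 3.3.4, apply patient exclusions (1), (2), (3), (5) and (7) and the 8-year education minimum to healthy participants. Exclusions (6) and (8) need not be carried over.
2. In Section 3.6.2, state that controls are frequency-matched to the aMCI group on age, sex and education.
3. In Section 3.11, compare aMCI with healthy participants by a linear model adjusted for age, sex and education, on transformed or ranked data where the variable is non-normal, in place of the unadjusted t-test or Mann–Whitney U test.

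**Cost.** A protocol amendment, slightly slower recruitment of 20 controls, and a few degrees of freedom out of 58. HAMD, HAMA and MRI are already scheduled for controls, and their general information is already recorded. If controls are already enrolled, use the adjusted analysis and report education, smoking, alcohol, medication and relevant medical history by group.

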### Randomization and assessor-blinding

3.4.

Patients with aMCI will be randomly divided into AG or WG according to the computer-generated random numbers. The random sequence with an identifying letter will be sealed in a light-tight envelope, which will be opened when eligible participants are enrolled. During the research process, the sequence generation and allocation will be performed by an independent person not participating in the trial. Healthy participants will be enrolled as the normal control without randomization.

Blinded evaluation will be conducted, and patients will be treated separately. The efficacy will be evaluated by a third person unaware of the group assignments; blinded statistical analysis will be used in the data summary stage, and the investigators, clinical operators, efficacy evaluators, and data statisticians will be separated throughout the whole study process.

### Sample size

3.5.

Previous studies (34, 35) have suggested that 15 participants should be included in each group to ensure a stable statistical effect for brain fMRI data analysis. In most similar studies (36–38) which used fMRI, gut microbiota, or inflammatory cytokines as indicators to explore the mechanisms of acupuncture, the sample size was mostly 15–20 participants per group. Thus, the sample size in our study will be 20 participants per group. Additionally, 20 healthy participants will be included.

### Intervention

3.6.

#### Patients with aMCI

3.6.1.

Patients in the AG will receive acupuncture treatment. Standardised acupuncture treatment will be based on the Standards for Reporting Interventions in Controlled Trials (STRICTA) (Table 2). The following acupoints will be used: Shenting (GV 24), Baihui (GV 20), Anmian (EX-HN 18), Shenmen (HT 7), and Taixi (KI 3). The orientation and manipulation of the acupoints will be performed based on TCM standards, as described in Figure 2. Licensed acupuncturists will use single-use sterile needles (Hwato, Suzhou, China; 0.25 × 25 mm) to insert acupoints after skin disinfection. Subsequently, twisting, thrusting, and rotation will be conducted by uniform reinforcing-reducing methods to create the experience termed De Qi within the range of patient tolerance. All needles will be manipulated manually every 10 min to maintain the De Qi sensation, the twisting angle will be 90–180 degrees, and the frequency will be 60–90 times/min, with an amplitude of lifting and inserting of 0.3–0.5 cm. The treatment will include 24–30 min sessions over 12 weeks.

**Table 2 tab2:** Acupuncture treatment details based on the STRICTA 2010 checklist.

Item	Item number	Detail
1. Acupuncture rationale	1a) Style of acupuncture	Traditional Chinese Medicine
	1b) Reasoning for treatment provided, based on historical context, literature sources, and/or consensus methods, with references where appropriate	The treatment is carried out according to traditional acupuncture theory, previous studies, and the experts’ consensus.
	1c) Extent to which treatment was varied	Standardised acupuncture treatment
2. Details of needling	2a) Number of needle insertions per subject per session	8
	2b) Names of points used	GV 20 (Baihui), GV 24 (Shenting), EX-HN 18 (Anmian), HT 7 (Shenmen), and KI 3 (Taixi)
	2c) Depth of insertion, based on a specified unit of measurement, or on a particular tissue level	From 15 to 25 mm.
	2d) Response sought	Deqi (numbness, soreness, heaviness, distention, etc.)
	2e) Needle stimulation	Manual acupuncture
	2f) Needle retention time	30 min
	2g) Needle type	Sterile, disposable acupuncture needles (length, 25 mm; diameter, 0.25 mm; Hwato, China).
3. Treatment regimen	3a) Number of treatment sessions	24 treatment sessions in acupuncture group.
	3b) Frequency and duration of treatment sessions	Twice per week (once per 2–3 days interval), for 12 continuous weeks.
4. Other components of treatment	4a) Details of other interventions administered to the acupuncture group	Dietary and lifestyle advice.
	4b) Setting and context of treatment, including instructions to practitioners, and information and explanations to patients	The trial will be implemented at departments (Chengdu Fourth People’s Hospital, Sichuan Provincial People’s Hospital, West China Hospital of Sichuan University, Sichuan Provincial Rehabilitation Hospital). All participants of acupuncture group will be arranged to the acupuncture & moxibustion room for treatment. All information and explanations will be provided to participants.
5. Practitioner background	5) Description of participating acupuncturists	Trained, licensed acupuncturists with at least 6 years in acupuncture clinical practice
6. Control or comparator interventions	6a) Rationale for the control or comparator in the context of the research question, with sources that justify this choice	The treatment is carried out according to previous studies, and the experts’ consensus.
	6b) Precise description of the control or comparator. If sham acupuncture or any other type of acupuncture-like control is used, provide details as for Items 1 to 3 above.	No acupuncture treatment in the waiting-list group during 12-week observation period after randomization. And dietary and lifestyle advice would be provided at each visit.

**Figure 2 fig2:**
[figure not shown]
Locations and manipulations of acupoints selected in this study: GV 20 (Baihui), 5 cun directly above the midpoint of the anterior hairline, at the midpoit of the connecting the apexes of the two auricles. Subcutaneous insertion to a depth of 0.5-1 cun with manipulation for the deqi. GV 24 (Shenting), 0.5 cun directly above the midpoint of the anterior hairline. Subcutaneous insertion to a depth of 0.3-0.5 cun with manipulation for the deqi. EX-HN 18 (Anmian), at the neck, the midpoint of the line between GB20 (Fengchi) and TE 17 (Yifeng). Subcutaneous insertion to a depth of 0.5-1 cun with manipulation for the deqi. HT 7 (Shenmen), at the ulnar end of the transverse crease of the wrist, in the depression on the radial side of the tendon of m. flexor carpi ulnaris. Subcutaneous insertion to a depth of 0.3-0.5 cun with manipulation for the deqi. KI 3 (Taixi), posterior to the medial malleolus, in the depression between tip of the medial malleolus and tendo calcaneus. Subcutaneous insertion to depth of 0.5-1 cun with manipulation for the deqi.

Patients in the WG will not undergo acupuncture treatment during the observation period, and they will be informed that 24 free acupuncture sessions can be provided to them after observation.

Both groups will receive 10–15 min of aMCI-related health education at each visit to improve their cognitive function. The health education content is referred to in the *Dietary and lifestyle guidelines for the Prevention of Alzheimer’s Disease,* published in *Neurobiology of Aging* in 2014 (39). During the trial, patients will be allowed to receive basic treatment, such as blood pressure control, glucose control, and other supportive care. The time, dose, frequency, and response to treatment will be recorded. Participants will also be advised to avoid using other medications that affect cognitive function or acupuncture, massage, application, etc. The clinician will formulate a corresponding treatment plan and make detailed records if the symptoms are severe.

#### Healthy participants

3.6.2.

The healthy participants will not receive any treatment. Matched healthy individuals without cognitive impairment will be determined based on their medical history and cognitive function tests. The general information and cognitive assessment results will be recorded. fMRI images, faecal samples and fasting blood samples of healthy participants will be acquired at enrollment.

### Primary outcome

3.7.

Changes in the Alzheimer’s Disease Assessment Scale-cognitive (ADAS-cog) score, assessed from the baseline to end of treatment, will be used to evaluate the cognitive function of patients. The ADAS-cog is designed as a rating scale for the severity of cognitive dysfunction in people with AD and comprises 12 subscales designed to assess several cognitive domains, including word recall and recognition, naming, instruction, language comprehension and expression, orientation, praxis, attention and other cognitive abilities. The total score is the sum of the scores of all subscales, with higher scores indicating greater cognitive impairment.

### Other outcome measures

3.8.

#### Changes in clinical symptoms

3.8.1.

The following clinical efficacy-related outcomes in patients with aMCI will be used for this study: improvement of cognition, daily living ability, mental behaviour, emotion, and sleep. These outcomes will be measured at baseline and after 12 weeks of the intervention. Each participant will be evaluated by a professional physician unaware of the intervention regimen. Medication combination, compliance, dropout, and elimination cases will be recorded.

The Auditory Verbal Learning Test – Huashan version (AVLT-H) scale will be adopted to evaluate the memory function of patients. It is an objective test proven to be a sensitive measure for diagnosing aMCI (40). The word list consists of 12 two-character Chinese words from three semantic categories (flowers, occupations, and apparel), with four words in each category. The AVLT-H score is allocated as follows: (1) the immediate recall total score representing verbal working memory; (2) the short-term and long-term delayed recall score expressing recall memory; (3) the category-cued recall score; and (4) the recognition score. Considering that delayed recall memory is the first domain to be impaired in individuals with MCI (41), we will measure the changes in long-term delayed recognition scores in this study. The higher the score, the better the memory function.

The Montreal Cognitive Assessment-Basic (MoCA-B) scale will be used to evaluate the cognitive function of patients. The MoCA-B scale is an effective cognitive tool for detecting MCI among older Chinese individuals across all education levels (41). The MoCA-B assesses nine cognitive domains (executive function, language, memory, attention, orientation, calculation, concentration, conceptual thinking, and visual perception) with a total score of 30. The cut-off score for MCI is 16–22 for individuals with mid-level education and 17–24 for those with high-level education. The lower the score, the worse the cognitive function.

The FAQ will be used to evaluate the daily living ability of patients. It is a 10-item measure of difficulties in activities of daily living (42); each item is rated from 0 (no difficulty or independent) to 3 (dependent). The total severity (total sum score from all 10 items, range 0–30) reflects the extent of functional impairment. A total score > 9 indicates impairment of daily living ability; the higher the score, the lower the daily living ability.

The HAMD and HAMA scales will be used to evaluate the emotional status of patients. Anxiety and depression have been identified as risk factors for progression from aMCI to AD dementia (43). Approximately 90% of patients with AD have a variety of psychiatric symptoms, of which depression is the most common type (44, 45). The HAMD scale comprises 17 items that measure somatic and affective symptoms of depression. Each item is scored for severity on a scale of 0–4, with a higher score reflecting higher symptom severity. A total score of 0–7 is generally considered normal; ≥ 7 points indicate probable depression; ≥ 17 points, depression; and ≥ 24 points, severe depression. The HAMA scale comprises 14 items, and each item is rated from 0 (absent) to 4 (severe enough to affect daily life). The total score is the sum of the individual scores of the 14 items. The scoring standards for HAMA are: < 7 points, no anxiety; ≥ 7 points indicate probable anxiety; ≥ 14 points, anxiety; and ≥ 29 points, severe anxiety.

The Mild Behavioral Impairment Checklist (MBI-C) scale will be used to evaluate the mental behaviour of patients. Mild behavioural impairment (MBI) has been proposed as an early manifestation of dementia. The MBI-C is a reliable tool for identifying psychological and behavioural changes in patients with MCI (46). It includes 34 items organised in five domains (decreased motivation, affective dysregulation, impulse dyscontrol, social inappropriateness, and abnormal perception and thought). For each item, a “yes” or “no” question is followed by a severity rating scale of 1 – mild, 2 – moderate, or 3 – severe. MBI-C is especially useful for detecting MBI in people with MCI; the total score is the sum of scores of 34 items, with higher scores indicating the worse MBI.

The Pittsburgh Sleep Quality Index (PSQI) will be used to assess the sleep quality of the participants in the last month before and after the intervention. Sleep disturbances are common in people with MCI and may accelerate MCI progression (47). The PSQI provides a global sleep quality score based on seven components (sleep quality, latency, duration, efficiency, disturbance, use of sleep medication and daytime dysfunction). The sum of scores for these seven components yielded one total score. A global PSQI score > 5 is considered poor sleep quality.

